**Fig. 2 Fig2:**
[figure not shown]
Power by prevalence reduction by country (Burkina Faso and The Gambia)

As for the incidence of infection, this will be determined by collecting monthly blood samples from randomly selected individuals. In The Gambia, in 2013–2014, the incidence of infection in the study area was 1.42 per person-year [14]. In Burkina Faso, the incidence of infection is assumed to be at least twofold higher, i.e. 2.8 per person-year. Applying the same assumptions for the primary endpoint (e.g. ICC), 20 individuals per village in Burkina Faso and 30 in The Gambia will be able to detect a 38% reduction in the incidence of infections at 80% power. This estimation considers the number of clusters both in Burkina Faso and The Gambia (Fig. 3).

**Fig. 3 Fig3:**
[figure not shown]
Reduction of incidence rate detected by sample size at 80% power

The primary outcome, prevalence of malaria infection, defined as the proportion of sampled residents carrying the parasite (*P. falciparum*) detectable by varATS PCR, will be compared between study arms using random effects logistic regression (with random effect on village) adjusting for study month, age group (< 5, 5–15 and > 15), ITN use and baseline malaria prevalence by village.

For secondary outcomes, incidence of clinical malaria will be estimated by recording all clinical cases from study villages (both intervention and control) attending the local health facilities or diagnosed by study nurses based in study villages (passive case detection). Incidence will be compared between arms using random effects Poisson regression—a random effect for study village will be included for the clustering. Incidence of malaria infection will be estimated by the number of first or only infections over person-months of follow-up. Intervention coverage will be measured by dividing the number of individuals having completed the vaccination schedule (3 monthly doses) by the number of individuals eligible for vaccination. In addition, coverage of at least one vaccine dose will be estimated. Coverage will be calculated for each vaccination round and intervention year, while community acceptability will be assessed qualitatively in both the intervention and control arms. Vaccination costs and cost-effectiveness will be estimated by the annual costs of the vaccination campaign and the vaccine delivery cost per vaccinated individual. The cost-effectiveness will be estimated for the intervention (mass vaccination campaign) compared to the status quo (no mass vaccination campaign).

The exploratory outcome, the prevalence of serological markers (AMA-1, MSP-1, GLURP, GexP, RH2030 and Etramp5.Ag1), will be compared between arms using random effects logistic regression (with random effect on village).

Missing data percentages will be reported; available case analysis will be performed unless there is a higher missing data rate (> 15%) in which case we will consider using multiple imputation for the analyses. Primary analysis will be based on intention-to-treat approach; however, we will explore a treatment effect separately for those receiving the full dose as per the protocol and those receiving partial doses in sensitivity analyses.

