### Study population and eligibility criteria

The target population for the R21 mass vaccination campaign are all eligible residents in the intervention villages. Residents in intervention villages will be enrolled for vaccination according to well-defined inclusion criteria as follows: [1] age ≥ 5 months, [2] willingness to comply with trial procedures, and [3] individual written informed consent. Exclusion criteria include the following: [1] pregnancy, [2] history of allergic disease or reactions likely to be exacerbated by any component of the vaccines, [3] any history of anaphylaxis in relation to vaccination, [4] known chronic illness, [5] any other significant disease, disorder or situation which, in the opinion of the investigator, may either put the participants at risk because of participation in the trial, or influence the result of the trial, or the participant’s ability to participate in the trial. To be vaccinated, all inclusion criteria and none of the exclusion criteria should be met. Prior to each vaccine dose, women of reproductive age (15 to 49 years old) will be systematically tested for pregnancy. Moreover, eligibility will be checked for all study participants during each vaccination round, and before the administration of the vaccine dose.

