### Mass vaccination

The study intervention*, *i.e., mass vaccination with R21, will be implemented over 2 years in 2024 and 2025, covering two malaria transmission seasons. Three monthly doses of R21 (primo-vaccination) will be administered to all eligible residents in intervention villages, starting from May 2024, with the aim of completing the vaccination schedule by July 2024, before the start of the malaria transmission season. A booster vaccine dose will be administered the following year, in June 2025, to all eligible individuals who received at least one vaccine dose the previous year. Residents who are eligible but not vaccinated in the previous year will be offered a complete vaccination schedule, i.e. 3 monthly doses, starting from April 2025 (Fig. 1).

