## Discussion

The SERVAL trial aims to determine the impact of seasonal mass vaccination with R21 on malaria burden, i.e. prevalence of infection, incidence of clinical malaria and malaria infections. This is the first time the potential effect of vaccinating the entire population with a vaccine developed for children under 5 years of age is being investigated. While the R21 vaccine was first tested in adults before progressing to phase II and III trials in children [22], there remains limited data on its efficacy in protecting older children and adults from infection. The administration of R21 vaccines to healthy volunteers both in the United Kingdom (UK) and Burkina Faso was safe and elicited similar IgG immune responses against the conserved central NANP repeat region of the pre-erythrocytic CSP [23]. Furthermore, in adult volunteers who received the standard regimen of three doses of R21 at four-week intervals and were then experimentally infected with malaria, the vaccine demonstrated an efficacy of 80% [22]. Mathematical models suggest that mass vaccination with a pre-erythrocytic vaccine may substantially reduce population-level malaria transmission [5]. Mass vaccination before the transmission season at a coverage between 60 and 80% may reduce malaria prevalence by 70–80%, while combining it with mass drug administration would almost interrupt transmission [24]. It is important to confirm or refute such predictions through large-scale trials especially given that some goals outlined in the WHO Global Technical Strategy 2016–2030 are lagging by over 60% [25]. Urgent new control tools and strategies are needed to regain progress towards malaria elimination and eventual eradication. The mass vaccination of the entire population with R21 could be one such approach.

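### Coverage is divided by eligible individuals, but eligibility includes willingness and consent, so residents who refuse or are never reached for consent cannot lower the figure

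*Protocol article*

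**What the plan says.** The statistical analysis text of the protocol article (Sample size and statistical analysis, after Fig. 3) defines intervention coverage by "dividing the number of individuals having completed the vaccination schedule (3 monthly doses) by the number of individuals eligible for vaccination". It adds: "In addition, coverage of at least one vaccine dose will be estimated", without naming a separate denominator. On timing it says: "Coverage will be calculated for each vaccination round and intervention year".

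Eligibility is defined once, under Study population and eligibility criteria. The inclusion criteria are a minimum age of 5 months and "willingness to comply with trial procedures, and [3] individual written informed consent". All inclusion criteria and no exclusion criterion must be met before vaccination, and "eligibility will be checked for all study participants during each vaccination round, and before the administration of the vaccine dose".

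Village selection and Informed consent describes a census of the study villages, followed by written consent from residents who are willing. Each resident receives a unique census number. Consenting continues through the trial for new residents and for those missed at first.

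Mass vaccination gives the 2025 booster "to all eligible individuals who received at least one vaccine dose the previous year". Eligible residents left unvaccinated in 2024 are offered the three-dose course.

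Coverage is a secondary endpoint (Study outcomes) and part of a secondary objective, together with its socio-cultural determinants (Trial objectives).

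**The concern.** The Discussion expects vaccine hesitancy and population movement to depress coverage, possibly far enough to leave little or no effect. A coverage measure for this trial therefore has to fall when people refuse. With willingness and consent inside the definition of eligibility, a refusal removes the person from numerator and denominator alike, and the ratio does not move. The same holds for a resident the team never reached for consent.

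Coverage is what a reader will turn to if the prevalence difference is small or absent, to judge whether the vaccine had little effect on transmission or too few people took it. A ratio conditional on consent would point towards the first explanation even where refusal was common.

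The numerator raises a second, smaller problem. Coverage is to be given for each round and each year, but the only numerator defined for the main measure is completion of three monthly doses. That cannot be evaluated at round 1 or 2, and it does not describe the booster year for most vaccinees.

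**Working it through.** The document states no coverage figure, coverage target, consent rate or refusal rate, so there is no plan figure to reproduce. The check is algebra on the stated definitions, with assumed inputs marked as such.

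**Definitions**
- E: residents of intervention villages who meet the age and medical criteria.
- r: the share of E who refuse or are never reached for consent (not stated; assumed 10–40%).
- c: three-dose completion among those who consent (not stated; assumed 70–90%).

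**Formulas**
- Completers = c × (1−r) × E.
- Denominator as written (consent required) = (1−r) × E, so reported coverage = c, whatever r is.
- Denominator with refusers and unreached residents kept in = E, so coverage = c(1−r).
- Overstatement = c − c(1−r) = c × r points; ratio = 1/(1−r).

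**Results**

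| c (reported) | r = 10% | r = 20% | r = 30% | r = 40% |
|---|---|---|---|---|
| 70% | 63% | 56% | 49% | 42% |
| 80% | 72% | 64% | 56% | 48% |
| 90% | 81% | 72% | 63% | 54% |

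The cells give coverage among all of E. The overstatement runs from 0.70 × 0.10 = 7 points to 0.90 × 0.40 = 36 points, and is zero only if r = 0.

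**One assumed village**
- 400 residents, 40 of them ineligible by age or health: E = 360.
- 72 refuse or are never reached (r = 72/360 = 20%), leaving 288 who consent.
- At 80% completion, about 230 complete three doses.
- As written: 230/288 = 79.9%.
- Age- and medically eligible: 230/360 = 63.9%.
- All residents: 230/400 = 57.5%.

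**Numerator in 2025.** A person with at least one dose in 2024 is due one booster. If completion means three doses within 2025, everyone who received the booster as planned is missed and only the catch-up group can count. If it means three doses ever, a 2024 completer counts in 2025 whether or not the booster was given. Neither reading measures receipt of what was due that year.

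**The case against.** The strongest reply is that the authors probably do not mean the strict definition. Mass vaccination speaks of residents who are eligible yet went unvaccinated in 2024 and will be offered the full course in 2025; a catch-up that left out people who declined or were missed would have little purpose. The Discussion links accurate coverage to regular census updates and expects hesitancy to lower coverage, which makes sense only if refusers are counted. This stands as evidence of intent. It does not settle the definition: the analysis text never names the census as denominator, and the only list of eligibility criteria includes consent. The word carries two meanings, and the formula does not say which applies.

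Three stronger readings are tempting, and the document does not support them.

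- *All absentees drop out.* Consent is sought after the census and before study procedures, not at the injection. A person who consented and then missed a round remains in the three-dose denominator as a non-completer. Only residents never reached for consent are lost. For round-specific figures the position is unclear, because eligibility is re-checked at the round itself.
- *At-least-one-dose coverage is near 100% by construction.* A consented person who never presents is a zero-dose member of the denominator. Nothing fixes the figure near 100%.
- *A coverage target would wrongly appear to be met.* The Discussion cites modelling of "Mass vaccination before the transmission season at a coverage between 60 and 80" per cent, but as background. It does not state the denominator behind that range, and the protocol sets no target and plans no comparison with it.

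It is also fair to say that the booster round would get its own figure, that this is one descriptive secondary endpoint, and that a journal article condenses a longer protocol. But the article does not leave the formula to another document. It states one, and that formula conflicts with its own eligibility section.

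**Conclusion.** The point holds as a definitional defect in a secondary endpoint. On the article's own wording, refusal and failure to reach residents for consent cannot lower reported coverage, although the Discussion names hesitancy as a main threat to it. The direction and the factor 1/(1−r) follow from the definitions. The size does not: 7 to 36 points rests wholly on assumed values of r and c, and the true excess could be smaller if nearly everyone consents. If the authors intend the looser sense of eligible, there is no overstatement, but the text must then say so.

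The 2025 numerator needs no assumed rate: three-dose completion is not the course that people dosed in 2024 are due.

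A reader might infer that the main result is affected. It is not. The November surveys sample residents regardless of vaccination status, and the primary analysis is by intention to treat. What is at risk is the interpretation of that result.

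**What to change.** Reconcile the analysis text, the eligibility section and the mass vaccination section as follows.

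1. **Denominator.** All census residents of intervention villages who meet the age and medical criteria at the start of each year's campaign, irrespective of willingness, consent or presence.
2. **Second line.** Coverage over all census residents, with refusals and absences listed separately so that hesitancy and mobility can each be seen.
3. **Numerator for 2025.** Completion of the course due to each person under the existing schedule: booster, or three-dose catch-up.
4. **Round-specific coverage.** Receipt of that round's dose.

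The first line describes delivery to those who could be vaccinated, and the second describes protection of the village population. Both are useful and should be labelled as such.

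The change is one of wording: the census and its identification numbers are already planned. The cost is that the reported coverage figure will be lower.

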#### Randomisation and blinding

Randomisation will be stratified by country. The unit of randomisation will be the village (cluster) with about 200 to 600 inhabitants. Allocation of each of the selected villages to one of the trial’s arms (intervention/control) will be done through computer-based randomisation by the study’s statistician. To prevent imbalance for potential confounding factors, restricted randomisation to balance the arms on factors such as baseline prevalence, ITN coverage, and distance from health facilities will be used [20].

In this cluster-randomised trial, blinding residents to vaccination (*i.e.,* placebos) would not be justified considering the logistical challenges and costs, and the likely limited impact on outcome measures. Nevertheless, all laboratory staff involved in processing samples and evaluations contributing to the study outcomes will be blinded to the allocation arm (intervention or control arm).

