### Sample size and statistical analysis

The primary analysis will be a comparison of the cluster level malaria prevalence rates following the primo-vaccination (3 doses) between the two arms. Arms will initially be compared by a two-samples one-sided *t*-test (2.5%), and, to be conservative, the variance between prevalence in each arm will be assumed unequal (Welch approximation). The intra-cluster correlation coefficient (ICC) is estimated at 0.17 for Burkina Faso [19] and at 0.10 for The Gambia [15]. The malaria prevalence in the control arm is assumed to be 40% in Burkina Faso and 13.5% in The Gambia [15]. Assuming malaria prevalence in the intervention arm will decrease by about 45% compared to the control arm, 12 cluster per arm in Burkina Faso and 15 cluster per arm in The Gambia with 100 individuals per cluster would be needed to detect such a reduction between study arms with 80% power and a 5% significance level. The sample size has been estimated for each country separately as the impact of the intervention may differ between countries (Fig. 2).

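### Country is the randomisation stratum and the sizing unit, but no between-arm efficacy analysis is said to be run by country or to include country

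*Protocol article*

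**What the plan says.** Under Randomisation and blinding, the protocol article states: "Randomisation will be stratified by country". The village selection section adds that allocation is 1:1 in each country.

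Under Sample size and statistical analysis: "The sample size has been estimated for each country separately as the impact of the intervention may differ between countries". The inputs are also country-specific: "The malaria prevalence in the control arm is assumed to be 40% in Burkina Faso and 13.5% in The Gambia", with an ICC of 0.17 and 0.10 respectively. The caption of Fig. 2 describes power by country.

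The between-arm analyses in the same section are described once each, without reference to country:

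- **Primary test.** "Arms will initially be compared by a two-samples one-sided" t-test at 2.5% on village prevalences, with the Welch approximation.
- **Primary regression.** A logistic model with a village random effect. Its covariates are study month, age group, "ITN use and baseline malaria prevalence by village".
- **Clinical malaria.** A Poisson model in which "a random effect for study village will be included for the clustering"; no covariates are named.
- **Serology.** A logistic model with a village random effect only.

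Only cost and cost-effectiveness are said, in the Discussion, to be estimated in each study site.

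**The concern.** A factor that restricts the allocation, and that strongly predicts the outcome, belongs in the analysis. If it is left out of a pooled two-sample test, the estimated difference is still balanced on country, but the test's standard error is computed as though it were not. The test becomes conservative and gives up power.

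There is also a question of what is estimated. With a 45% reduction in both places, the absolute difference is 18 points in Burkina Faso and about 6 in The Gambia. A single pooled difference describes neither, and does not answer the per-country question on which the trial was sized. The Discussion says both countries were included because the vaccine's impact may vary with transmission intensity, but no comparison of the effect between countries is described.

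**Working it through.** **Inputs** (Sample size and statistical analysis). Control prevalence 0.40 (Burkina Faso, BF) and 0.135 (The Gambia, GM); 45% reduction, giving 0.22 and 0.07425; ICC 0.17 and 0.10; 12 and 15 villages per arm; m = 100 per village; one-sided 2.5%. The 5% level in the sample size statement is taken as two-sided.

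**Variance of a village prevalence.** p(1−p)[1+(m−1)ICC]/m:

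| | BF | GM |
|---|---|---|
| Control | 0.24 × 17.83/100 = 0.0428 | 0.1168 × 10.9/100 = 0.0127 |
| Intervention | 0.1716 × 17.83/100 = 0.0306 | 0.0687 × 10.9/100 = 0.0075 |

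**The plan's own figure.** The article states 80% power in each country. The Welch test by noncentral t gives:

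- BF: SE = √[(0.0428+0.0306)/12] = 0.0782; 0.18/0.0782 = 2.30; power 59%.
- GM: SE = √[(0.0127+0.0075)/15] = 0.0367; 0.06075/0.0367 = 1.65; power 36%.

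The stated 80% is not reproduced. That is a separate sample-size matter and is not the point here.

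**Pooled test, 27 against 27 villages.**

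1. Within-country variance, averaged over villages. Control: (12×0.0428+15×0.0127)/27 = 0.0261. Intervention: (12×0.0306+15×0.0075)/27 = 0.0178.
2. Between-country variance. Control: (12/27)(15/27)(0.265²) = 0.0173. Intervention: (12/27)(15/27)(0.14575²) = 0.0052.
3. Inflation of the error variance. Control arm, or both arms under the null: 0.0173/0.0261 = 66%. Intervention arm under the assumed effect: 0.0052/0.0178 = 30%. Both arms together: (0.0173+0.0052)/(0.0261+0.0178) = 0.0225/0.0439, about 52%. The treatment of the n−1 divisor moves this within roughly 50–57%.
4. Pooled difference: (12×0.18+15×0.06075)/27 = 0.114.
5. True SE under stratified allocation: √(0.0439/27) = 0.0403. SE that the unstratified test uses: √{[0.0439+(27/26)×0.0226]/27} = 0.0499.
6. Power, normal approximation. Without country: Φ[(0.11375−1.96×0.0499)/0.0403] = 65%. With country: Φ(0.11375/0.0403−1.96) = 81%.
7. Type I error without country. True SE √(2×0.0261/27) = 0.0440; SE used √{2[0.0261+(27/26)×0.0173]/27} = 0.0572; ratio 1.30. The effective critical value is 1.96×1.30 = 2.55, a one-sided tail of about 0.5%.

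**Simulation** with beta-binomial villages and t critical values (40,000 runs):

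| | Type I error | Power |
|---|---|---|
| Welch, no country | 0.6% | 64% |
| Linear model with country | 2.5% | 79% |

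Other runs gave 0.5–0.6% and 63–64% without country, and 2.5–2.7% and 78–79% with it. At a 30% reduction, power is 24% against 41%.

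**What baseline prevalence recovers.** A village-level linear model was used as a stand-in for the primary regression. The within-country correlation of baseline with outcome is an assumption.

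| Correlation | Baseline only | Baseline and country |
|---|---|---|
| 0 | 67% | 77% |
| 0.3 | 77% | 80% |
| 0.6 | 89% | 90% |

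**Poisson and serology models.** No figure was computed. If pooled, the country gap goes into the village random effect, since neither model lists a covariate to absorb it. For scale, the article assumes infection incidence of 1.42 and 2.8 per person-year; that clinical incidence differs similarly is an assumption.

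**The case against.** The strongest reply is that pooling is never stated. The article does not mention a 54-village test. The same section uses arm-comparison language for a calculation that is plainly per country, and the separate sizing and the by-country power figure both point to one test per country. On that reading country is constant within each test and leaving it out costs nothing. This stands: the loss is conditional on pooling. It does not remove the point, because the article never says that the comparison is by country.

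Second, the primary logistic model adjusts for baseline village prevalence. Villages enter at a baseline of at least 10% in The Gambia and at least 30% in Burkina Faso, so this covariate carries much of the country gap. This also stands. A reader might infer that every interval in the trial is widened; for the primary regression the documents do not support that.

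Third, even the pooled test without country (about 64%) is no weaker than the single-country tests recomputed above (59% and 36%). That is correct. The loss is relative to a stratified pooled analysis.

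Fourth, stratum terms are often left to the statistical analysis plan, which is not shown. That has some force for the secondary and exploratory models. It has less for the primary analysis, where the article itself names the test and lists the covariates, and the stratum is not among them.

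**Conclusion.** The point holds in conditional form. Country is the stratum and the sizing unit, and the described efficacy analyses neither include it nor say that they are run by country. If the t-test is pooled over 54 villages, one-sided type I error is about 0.6% and power about 64%, against about 2.5–2.7% and 78–79% with a country term. If it is run within each country, this loss does not arise. The loss applies to the unadjusted t-test and, in kind only, to pooled Poisson and serology models; the primary logistic model recovers part or nearly all of it.

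Two stronger readings should be resisted. One is that no analysis at all is by country: cost-effectiveness is estimated by study site. The other is that the 66% variance inflation applies under the assumed effect: it is the control-arm or null value, and the figure under the assumed effect is about 50–57%.

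The figures rest on the plan's prevalences and ICCs, a 45% reduction in both countries, 100 people per village and beta-distributed village prevalence.

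**What to change.** State that the primary comparison is made within each country, as sized, and that each country's result is reported in its own right. For any combined estimate, and for any pooled incidence or serology model, include country as a stratum or fixed effect and report the arm-by-country interaction. Country is known for every village, so the change needs no new data and costs only wording in the protocol or analysis plan.

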### Village selection and Informed consent

The year preceding the implementation of mass vaccination, a baseline cross-sectional survey will be conducted in November, at the peak of malaria transmission, to identify villages with the required malaria prevalence. The survey will be implemented in 45 Gambian villages in the URR and 30 Burkinabe villages in Boussé District. In The Gambia, 30 villages (clusters) with a baseline *Plasmodium falciparum* prevalence by qPCR of at least 10% will be selected and included in the study; for Burkina Faso, 24 villages with a baseline malaria prevalence of at least 30% will be selected and included in the study. In each country, selected villages will be randomised to either intervention or control arm in a 1:1 ratio using a computer-generated algorithm (R version 4.2.2 and STATA version 16). Randomisation will be constrained such that the mean baseline prevalence in the intervention clusters is within ± 10% of the prevalence in the control clusters.

Following a thorough explanation of the study objectives and methods to the local authorities and the population of the study villages through sensitisation meetings, a census will be conducted to determine the size of the population, age structure and use of standard malaria control interventions. Afterwards, the study team, including field workers and nurses, will initiate individual consent procedures (before any study-related activity is implemented) to obtain written informed consent from all willing residents. Parents/guardians will provide written informed consent for their children, while adolescents 12–17 years old will be asked to provide an additional written assent. The consenting process will continue during the trial to include new residents and those missed at the time of the initial consenting process. Each resident will be assigned a unique census identification number.

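### Allocation is restricted on baseline village factors, but the analysis named as primary is an unadjusted Welch t-test; if that test decides, it is conservative and forgoes power

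*Protocol article*

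**What the plan says.** **Design.** Under Randomisation and blinding: "Randomisation will be stratified by country", and "restricted randomisation to balance the arms on factors such as baseline prevalence, ITN coverage, and distance from health facilities will be used". Village selection and Informed consent gives one tolerance: "Randomisation will be constrained such that the mean baseline prevalence in the intervention clusters is within" ±10% of the control prevalence. It does not say whether that is relative or in percentage points. No tolerance is given for ITN coverage or distance.

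**Primary outcome.** Sample size and statistical analysis states: "The primary analysis will be a comparison of the cluster level malaria prevalence rates following the primo-vaccination (3 doses) between the two arms". The next sentence begins "Arms will initially be compared by a two-samples one-sided" and goes on to a t-test at 2.5% with the Welch approximation. It mentions no covariates. The text after Fig. 3 compares the same outcome by random effects logistic regression "adjusting for study month, age group", ITN use and baseline village prevalence. Distance from health facilities is not in that list.

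**Clinical malaria.** "Incidence will be compared between arms using random effects Poisson regression", with a village random effect. No covariates are listed.

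**The concern.** Restricted randomisation discards allocations in which the arms differ on the chosen factors. If those factors predict the outcome, the arm difference varies less over the permitted allocations than under simple randomisation. An unadjusted t-test does not see this. It estimates its standard error from the full between-village spread, including the part explained by the balanced factors. The standard error is then too large, the true alpha falls below nominal, and the precision that adjustment would give is not collected.

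With 24 villages in Burkina Faso and 30 in The Gambia, analysed by country, precision is scarce. What is at stake is a false negative or an unduly wide interval. It is not a false positive.

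**Working it through.** **Inputs from the article.** Control prevalence 40% (Burkina Faso) and 13.5% (The Gambia); 45% reduction, to 22% and 7.425%; ICC 0.17 and 0.10; 12 and 15 villages per arm; 100 people per village; one-sided 2.5%.

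**1. The plan's own power figure.** The variance of one village prevalence is p(1−p)[1+99×ICC]/100.
- Burkina Faso: design effect 1+99×0.17 = 17.83. Variances are 0.24×17.83/100 = 0.0428 and 0.1716×17.83/100 = 0.0306. SE = √[(0.0428+0.0306)/12] = 0.0782. Standardised difference 0.18/0.0782 = 2.30. Welch power is 59%.
- The Gambia: design effect 1+99×0.10 = 10.9. Variances are 0.0127 and 0.0075. SE = √[(0.0127+0.0075)/15] = 0.0367. Standardised difference 0.06075/0.0367 = 1.65. Welch power is 36%.

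The stated 80% does not reproduce. That is a separate matter, but it leaves little room for an inefficient test.

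**2. Expected direction.** If balance were exact and the village correlation between baseline and follow-up were ρ, the true SD of the arm difference would be √(1−ρ²) times what the unadjusted SE estimates. In the normal approximation the true one-sided alpha is Φ(−1.96/√(1−ρ²)):
- ρ = 0.5: 1.96/0.866 = 2.26, alpha 0.012.
- ρ = 0.7: 1.96/0.714 = 2.74, alpha 0.003.

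Balance within a tolerance is looser than exact balance, so real values lie between these and 0.025.

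**3. How tight the tolerance is.** The SE of the baseline arm difference, using the control variances above, is √(2×0.0428/12) = 0.084 in Burkina Faso and √(2×0.0127/15) = 0.041 in The Gambia. Read as relative, ±10% is 4 points (0.47 SE) and 1.35 points (0.33 SE). Read as percentage points it is 1.2 SE and 2.4 SE. In The Gambia that second reading barely restricts anything.

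**4. Simulation.** Village prevalences were beta-distributed at the stated ICCs, with allocation redrawn until the constraint on mean baseline prevalence was met. The Welch test was compared with a village-level regression on baseline prevalence (20,000 runs for the relative reading, 10,000 for points). ρ is assumed; the article gives no value.

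| Reading of ±10% | ρ | Burkina Faso: t-test alpha | Burkina Faso: power, t-test v adjusted | The Gambia: t-test alpha | The Gambia: power, t-test v adjusted |
|---|---|---|---|---|---|
| relative | 0 | 0.027 | 58% v 58% | 0.024 | 37% v 37% |
| relative | 0.3 | 0.023 | 58% v 62% | 0.020 | 37% v 40% |
| relative | 0.5 | 0.014 | 60% v 70% | 0.015 | 36% v 45% |
| relative | 0.7 | 0.006 | 60% v 82% | 0.007 | 33% v 55% |
| points | 0.3 | 0.021 | 59% v 62% | 0.023 | 37% v 39% |
| points | 0.5 | 0.015 | 59% v 69% | 0.022 | 37% v 43% |
| points | 0.7 | 0.011 | 59% v 81% | 0.020 | 37% v 53% |

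Under the relative reading the adjusted test held 0.023 to 0.027 in Burkina Faso. Repeat runs put the relative-reading gap at ρ = 0.7 between 17 and 23 points.

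**5. Poisson model.** Assumed Gambian inputs: 15 villages per arm, about 26 cases per village, village CV 0.6, 38% reduction, ρ = 0.5, Wald test, 1,500 runs. The unadjusted one-sided alpha was 0.047 under simple randomisation and 0.029 under restriction. With adjustment for baseline prevalence under restriction it was 0.043. Power under restriction was 63% unadjusted and 71% adjusted. Part of those 8 points reflects the adjusted test's higher alpha. Under simple randomisation, where the two alphas are close (0.047 and 0.045), the gap was 63% v 70%.

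**The case against.** The strongest reply is that the article already has an adjusted analysis of the primary outcome. The logistic model includes baseline prevalence, the one factor with a stated tolerance, and ITN use, and the t-test is only the comparison made initially. This stands. A reader might infer that the trial never recovers its design balance for the primary outcome; the text does not support that. The loss arises only if the t-test decides, and the article leaves that open while attaching the term primary analysis to the comparison made by the t-test.

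A reader might also infer that every unadjusted model here is over-conservative. The check does not show this for the Poisson model. Its alpha under restriction was about 0.029, because restriction offset a small-sample excess of the Wald test.

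Nor does restriction itself cost much power: in Burkina Faso t-test power stays at 58% to 60% at every correlation tried. The gap is mostly gain forgone by not adjusting.

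Three further points stand. The two descriptions of the restriction do not contradict each other, since one gives a tolerance for a factor that the other lists among examples. Distance need not strongly affect case detection, because study staff are stationed in every village. Covariates for secondary models may be set in an analysis plan that is not shown. The error is also in the conservative direction.

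What remains is that the article labels an unadjusted comparison as primary after restricting allocation on predictors of the outcome, and that its adjusted model omits one named restriction factor.

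**Conclusion.** The point holds in limited form. If the Welch test decides, and ±10% is relative, true one-sided alpha is about 0.015 at ρ = 0.5 and 0.006 to 0.007 at 0.7. Power is then 9 to 10 and about 17 to 23 points below an adjusted analysis. At ρ = 0 there is no loss, and at 0.3 it is 3 to 4 points. If ±10% means percentage points, the conservatism in The Gambia is slight (alpha 0.020 to 0.023). The power forgone there is 2, 6 and 16 points at ρ = 0.3, 0.5 and 0.7.

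These sizes rest on the assumed correlation, the stated ICCs and prevalences, and restriction on baseline prevalence alone. The simulation did not model the selection of villages above a baseline threshold (10% or 30%), which could narrow the baseline spread and lower the correlation.

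For the logistic model the gap is the absence of distance. For the Poisson model it is forgone precision, of a size that depends on inputs the article does not give.

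**What to change.** 1. State that the adjusted analysis of the primary outcome decides, and report the Welch test as supportive.
2. Include in it the village-level restriction factors actually used, as measured before allocation: baseline qPCR prevalence, ITN coverage and distance from health facilities. Say that the ITN restriction covariate is baseline village coverage. ITN use is listed without a time point, and the November survey also records preventive measures after randomisation.
3. Use the same factors in the infection and clinical malaria incidence models and in the year-2 prevalence model.
4. Add a small-sample correction to all of them, such as a t reference with between-village degrees of freedom or a randomisation test over the permitted allocations.
5. State whether ±10% is relative or in percentage points, and record the other factors and tolerances that were applied.

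Cost: wording in the analysis plan, settled before any arm comparison is seen. The restriction factors had to be known before allocation, so no new data are needed. Two or three degrees of freedom are spent out of 2×12−2 = 22 in Burkina Faso or 2×15−2 = 28 in The Gambia.
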